## 11.5 Annual reporting of suspected serious adverse reactions to CA and EC

SSI is responsible for submitting annual safety update reports on **unblinded** suspected serious adverse reactions, including all SUSARs to the EC and the CA (MHRA) as electronic documents on disc to the EC and MHRA.

The MHRA address to be used is:

### Information Processing Unit, Area 6

Medicines and Healthcare products Regulatory Agency, MHRA

[name]

[name]

Vauxhall

[name]

Great Britain

Annual Safety Reports should be prepared at yearly intervals from the date of the CTA approval and be submitted within sixty (60) days. If the clinical trial is ended before the first yearly Annual Safety Report should have been prepared, a safety report shall be prepared within ninety (90) days of the end of the trial, together with the end of trial notification.

The Department of Regulatory & Medical Affairs, SSI will be responsible for distributing blinded copies of these annual safety reports to the principal investigator, site responsible investigator(s) and the clinical trial manager at SSI.

The blinded SUSAR reports will be filed in the trial master file by SSI and in the investigator's file by the investigator/monitor.

## 12 Data management and statistical analysis

### 12.1 General considerations

A milestone in the clinical development of C-Tb is to determine on optimal cut-off value for the skin test. The cut-off value is defined as the smallest induration diameter that will result in a positive C-Tb "diagnosis". That is, a person is considered C-Tb positive (C-Tb+) if the induration is  $\geq$  cut-off and C-Tb negative (C-Tb) if the induration is  $<$  cut-off.

If a TB patient (latent or active) is denoted as TB+ and a TB-healthy person as TB the performance of a diagnostic test like C-Tb is quantified by its sensitivity, i.e.,  $\text{Prob}\{ \text{C-Tb}^+ \mid \text{TB}^+ \}$  and by its specificity,  $\text{Prob}\{ \text{C-Tb}^- \mid \text{TB}^- \}$ .

A low cut-off value implies a high sensitivity and a low specificity; and a high cut-off value implies a low sensitivity and a high specificity.

Together with a concurrent C-Tb study in recently diagnosed TB patients (TESEC-04) the data from the present study will contribute to define an optimal cut-off value, balancing sensitivity and specificity.

If  $F^-(x) (= \text{Prob}\{\text{induration} \leq x\})$  denotes the (theoretical) distribution function of the induration in a  $TB^-$  population the specificity of the C-Tb skin test is  $F^-(\text{cut-off} - 1)$ .

If  $F^+(x) (= \text{Prob}\{\text{induration} \leq x\})$  denotes the (theoretical) distribution function of the induration in a  $TB^+$  population the sensitivity of the C-Tb skin test is  $1 - F^+(\text{cut-off} - 1)$ .

The main objective in the present trial is therefore to estimate the distribution function  $F^-$ .

The Biostatistics Unit at SSI will be responsible for the data management and the statistical analysis of the trial data.

## 12.2 Data management

Clinical data is collected in the CRFs. The subject diaries are considered supportive for the investigators when filling in the CRFs, i.e. only relevant information from the diaries will be transferred to the CRFs by the investigator. The diaries will not be sent to the sponsor's site but will remain filed at the investigator's site and filed with the investigator's copy of the CRFs.

SSI will receive laboratory data as signed printouts from the investigator. The printouts are identified by subject number and date of blood sampling.

Data from the CRFs and from laboratory records will be entered into SAS data sets and checked for consistency and plausibility by custom-made SAS programs. All ambiguous or implausible data items will be resolved by data queries to the investigator. When these findings have been resolved the SAS data sets will be copied to CDs, an audit trail established for the SAS data sets, and printouts of the datasets are proofread against the CRFs and laboratory printouts for the SAS data sets.

## 12.3 Clean file procedures

After correction of any errors found in the proofreading process, the SAS data sets reach clean file status. The SAS data sets will then be copied to CDs. Two identical sets of CDs will be made. One CD will be archived in the trial master file. The other CD will be archived at the Biostatistics unit at SSI.

The statistical analysis reported in the integrated clinical trial report will be based on the clean file data.

## 12.4 Analysis populations

The safety analysis population consists of all subjects who have received at least one TST (C-Tb or PPD) in the trial.

As the focus in this trial is on estimation of  $F^-(x)$  the efficacy population will be a pure “per protocol population” meaning that only those subjects who meet the inclusion criteria and have an induration measurement on day 2 or 3 after the injections are included in the estimation.

## 12.5 Statistical methods

The protocol allows reading of the induration to take place on day 2 or day 3. To investigate the influence of the time of reading the induration the correlations between time of reading (hours since injection) and induration diameters are assessed by Spearman’s rank correlation coefficient.

The induration diameters after the PPD skin test are compared with those after C-Tb by means of Spearman’s rank correlation, Wilcoxon’s signed rank test and supplemented with scatter plots.

Similarly the inclusion QuantiFERON®-TB Gold values are correlated with the C-Tb indurations by means of Spearman’s rank correlation, supplemented with scatter plots.

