| Statistical methods:                                                                                                                                         | 
The main objective of the trial is to contribute information on the size of induration in a healthy BCG vaccinated population, which can be used to define an optimal cut-off point for a C-Tb skin test.
 
In the trial the specificity of C-Tb (Specx) as a function of x (the diameter of the induration in mm) will be estimated.
 
For each (integer) value of x, Specx is estimated by the relative frequency of volunteers in the trial with a C-Tb induration ≤ x mm. 95% confidence intervals for Specx are obtained as Specx ± 2 × √ (Specx × (1 - Specx) / n), where n is the number of validly included volunteers.
 
As BCG vaccinated healthy subjects are not supposed to get an induration when exposed to C-Tb no formal statistical comparison of induration sizes between C-Tb and PPD will be made.
 
The subjects will have their PPD indurations classified according to UK standards for PPD cut-off points: 0-5 mm, 6-14 mm and 15+ mm (The Green Book).
 
PPD is considered negative if the induration is < 6 mm.
 
www.dh.gov.uk/en/PublicHealth/Healthprotection/Immunisation/Greenbook/DH_4097254
 |                                             |

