# 8 Investigational plan

## 8.1 Overall design

This clinical trial is a single-centre phase IIa study designed to investigate the specificity of C-Tb under various definitions of cut-off in a double blind randomised, split-body study comparing 0.1  $\mu$ g/0.1 mL C-Tb with the reference agent 2 T.U. Tuberculin PPD RT 23 SSI (Each volunteer receives the C-Tb agent in one arm and the 2 T.U. Tuberculin PPD RT 23 SSI agent in the other arm). The two skin tests are administered in a double-blind manner to make topical readings of an induration, if any, as objective as possible.

The trial will be conducted at Surrey Clinical Research Centre, University of Surrey, Guildford, United Kingdom under the responsibility of Principal Investigator: [name] [name].

The primary objective of the trial is to assess the specificity of the C-Tb skin test agent defined as the relative frequency of subjects in a healthy population (i.e., no exposure to MTb) who have an induration response  $<$  cut-off after a C-Tb test.

The C-Tb skin test is developed from MTb specific antigens (ESAT-6 and CFP-10) which are not expressed by any of the BCG-strains and only by a few of the atypical mycobacteria (e.g., *M. kansasii*, *M. marinum*, *M. szulgai*). No skin reaction (induration) is therefore expected at the injection sites with C-Tb. PPD, however, has protein components that are shared by the BCG vaccine strains and many non-tuberculous/ environmental mycobacteria. Some skin reactions are therefore expected to occur after testing with 2 T.U. Tuberculin PPD RT 23 SSI in a trial population of BCG vaccinated individuals.

Both erythema and induration, if any, will be documented in the case record forms (CRFs) of the volunteers.

In addition to the above, the immune response will be evaluated together with an assessment of the safety of the C-Tb skin test agent.

The volunteers are monitored closely for the occurrence of immediate adverse reactions during the first hour after the injections.

Each trial volunteer will be followed 28 days after the skin test injections and is expected to complete a total of 4 trial visits, as follows:

- |                |                |                                                                                                                                                              |

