|----------------|----------------|--------------------------------------------------------------------------------------------------------------------------------------------------------------|
| Visit 1 | -              | Screening Visit - comprising a medical examination and blood tests for clinically safety parameters and the QuantiFERON ® -TB Gold In-Tube |
| Visit 2 | Day 0   | Inclusion Visit and Injection of skin tests (0-28 days after screening)                                                                               |
| Visit 3 | Day 2-3 | Assessment Visit                                                                                                                                      |
| Visit 4 | Day 28  | Final 28 day Visit - comprising a medical examination and blood tests for clinically safety parameters ( ± 2 days)                                    |

For practical reasons Visit 2 (Inclusion and injection) should always take place on a Monday, Tuesday, Wednesday or Friday (to allow follow-up 2 or 3 days after skin testing). For more details on the visits see Section 9.3.

QuantiFERON®-TB Gold In-Tube assay will be performed at the screening visit and on day 28. There is a small risk that this blood test can become positive during the trial due to the injected C-Tb skin test agent. Volunteers with a positive QFN test taken at the last visit (Visit 4) will therefore be offered an additional visit 6 months after the last visit in the trial to be re-tested with the QFN assay.

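### The only reading-time analysis named for C-Tb, a Spearman correlation, may be undefined or uninformative under the protocol's own expectation of no C-Tb induration

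*Protocol*

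**What the plan says.** Section 12.5 notes the two-day window: "The protocol allows reading of the induration to take place on day 2 or day 3". It then gives the purpose, "To investigate the influence of the time of reading the induration", and the method: "the correlations between time of reading (hours since injection) and induration diameters are assessed", with Spearman's coefficient as the measure. The sentence is not limited to one agent, so it covers both C-Tb and PPD. No other analysis of reading time appears in the protocol.

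Section 12.4 puts readings from both days into the primary estimate: subjects who meet the inclusion criteria and "have an induration measurement on day 2 or 3 after the injections are included in the estimation". It attaches no condition on the reading-time result.

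The expected data are described twice. Section 8.1: "No skin reaction (induration) is therefore expected at the injection sites with C-Tb". The Synopsis, under statistical methods: "As BCG vaccinated healthy subjects are not supposed to get an induration when exposed to C-Tb". The Synopsis uses this as its reason for making no formal comparison of C-Tb and PPD induration sizes. For PPD, section 8.1 does expect some reactions.

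Section 8.1 also fixes the injection days: Visit 2 "should always take place on a Monday, Tuesday, Wednesday or Friday".

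**The concern.** A rank correlation needs variation in both variables. The protocol expects almost none in C-Tb induration, so the named statistic suits poorly the agent whose specificity the trial estimates. If all readings are zero there is nothing to report, and the protocol gives no fallback. If only a handful are non-zero, the mass of ties at 0 mm limits how large the coefficient can be, even when every reaction falls on one day.

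Reading time is also close to a two-group variable. Thursday, the weekday left out for injections, is the one whose day 2 and day 3 are Saturday and Sunday. This suggests weekday reading, in clusters around 48 and 72 hours. The natural question is whether the proportion below a cut-off differs between the two days.

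At stake is interpretation: a small or missing coefficient could be taken as reassurance about reading day that the method cannot give.

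**Working it through.** **Inputs.** n = 150 (sections 8.3 and 12.6); two reading days (12.5); expected C-Tb induration 0 mm (8.1, Synopsis). The split between days and the number of reactors (non-zero readings), k, are not in the document. I assume 75 per day unless stated, and vary k.

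**The plan's own figure.** None is given for the reading-time check. The precision figure in section 12.6 reproduces: √(0.5 × 0.5 / 150) = 0.041.

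**All readings zero.** The ranks of induration have no variance, so the coefficient is 0/0. A run with 150 zeros returns no value. The chance of this is (1 − p)^150 for a true non-zero rate p:

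| Assumed p | Chance of all zeros |
|---|---|
| 0.5% | 47% |
| 1% | 22% |
| 2% | 4.8% |
| 5% | 0.05% |

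**Few reactors, all on one day.** This is the strongest day effect possible for a given k. With m volunteers read on that day, the tie-corrected coefficient against reading day is √[k(n − m) / ((n − k)m)], which is √[k / (150 − k)] for 75 and 75. The exact two-sided permutation p for that split is 2 × C(75, k) / C(150, k).

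| k | Coefficient against day | p, t approximation | p, exact |
|---|---|---|---|
| 2 | √(2/148) = 0.116 | 0.157 | 0.50 |
| 3 | √(3/147) = 0.143 | 0.081 | 0.24 |
| 4 | √(4/146) = 0.166 | 0.043 | 0.12 |
| 5 | √(5/145) = 0.186 | 0.023 | 0.058 |
| 10 | √(10/140) = 0.267 | 0.001 | 0.001 |

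The two-sided 5% critical value from the t approximation is 0.160.

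**Other splits, k = 5.** If the reactors' day has 50 volunteers, √[5 × 100 / (145 × 50)] = 0.263. If it has 100, √[5 × 50 / (145 × 100)] = 0.131.

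**Hours instead of days.** With untied hours the ceiling is about √[3k(n − k) / (n² − 1)]: 0.199, 0.311 and 0.432 for k = 2, 5 and 10. Reaching it requires the reactors to be the k latest (or earliest) of all 150 readings, which is more than a day effect. If five reactors sit at random hours within day 3, their mean time rank is 113 against 75.5 overall. The rank standard deviation is √[(150² − 1)/12] = 43.3, so the expected coefficient is (37.5 / 43.3) × 0.186 = 0.161.

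**Power.** Simulated with hours, 75 per day, 3,000 runs, and assumed non-zero rates on day 2 against day 3: 8% for 1% v 3%; 18% for 1% v 5%; 28% for 2% v 8%; 57% for 1% v 10%.

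**The alternative.** Newcombe's score interval combines the Wilson limits of each day.
- 0/75 on both days: Wilson upper limit 3.84 / (75 + 3.84) = 4.9%, so the difference is 0 with limits ±4.9 points.
- 5/75 against 0/75: difference 6.7 points. The Wilson limits are 2.9% to 14.7% and 0 to 4.9%. Lower limit 6.7 − √[(6.7 − 2.9)² + 4.9²] = 0.5; upper limit 14.7.

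**The case against.** A reader might infer that the method cannot show a reading-time effect at all. That goes too far. A coefficient has to be judged against its null distribution, not against 1, and with ten reactors all on one day it detects the effect (p = 0.001). The t approximation already passes 5% at four and five reactors, but the exact p-values for those splits are 0.12 and 0.058, so that apparent advantage is not real.

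A reader might also infer that pooling the two days rests on this check. The text does not say so. Section 12.4 pools regardless, section 12.5 speaks only of investigating, and the endpoint itself is a reading at 2–3 days.

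Three further objections have force. The check also covers PPD, where reactions are expected and the coefficient works, although a PPD result does not automatically carry over to C-Tb. The replacement does not overcome rare events: at four reactors on one day its interval is −0.5 to 12.9 points and includes zero. And where the coefficient degenerates, specificity is near 1 on both days, so little is lost.

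The last objection is that tabulation by day, and what to do with an incalculable statistic, belong in the SAP, which is not shown. This stands only in part: the protocol itself fixes the statistic by name.

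**Conclusion.** The point holds in a limited form and is minor. For C-Tb, the one named reading-time analysis is undefined if all readings are 0 mm, which is the result the protocol expects. With few reactors it is bounded well below 1 (0.116, 0.186 and 0.267 for 2, 5 and 10, with 75 per day and all reactors on one day) and has little power. A missing or small C-Tb coefficient is therefore no evidence that reading day is unimportant. The primary estimate does not formally depend on it.

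The day split, reactor counts and reaction rates are assumptions. Between 50 and 100 volunteers on the reactors' day, the five-reactor figure ranges from 0.263 to 0.131. That the coefficient is undefined with all zeros needs none of these assumptions.

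**What to change.** In section 12.5, replace the C-Tb correlation by the specificity at each candidate cut-off for day-2 and day-3 readings separately, with the difference and a score-based (for example Newcombe) 95% confidence interval. This is on the scale of the primary objective, stays defined at zero counts, and shows the reader how large a difference the data leave open. Keep Spearman's correlation with hours since injection for PPD.

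The cost is one changed sentence and one extra table, with no new data. The downside is that the intervals will be wide when reactions are rare. That reflects the information available and should be reported as such.

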## 7.2 Secondary objectives

- To compare the induration response of C-Tb with the induration response of 2 T.U. Tuberculin PPD RT 23 SSI
- To compare the induration response of C-Tb with the in-vitro IFN- $\gamma$  response measured at screening and 28 days after the injections of the skin test agents using the QuantiFERON®-TB Gold In-Tube assay
- To record all adverse events occurring within 28 days after application of the agents

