## 7.4 Secondary endpoints

- Injection site adverse reactions within 28 days after application of the agents
- All adverse events occurring within 28 days after application of the agents
- Laboratory safety parameters of haematology and biochemistry
- *In vitro* IFN- $\gamma$  response as measured by the QuantiFERON®-TB Gold In-Tube assay from blood samples taken at screening and 28 days after the injections of the skin test agents

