## **8.2 Study population and organisation of the clinical trial**

Female/male BCG vaccinated adults aged 18 - 65 with an IFN- $\gamma$  result below 0.35 IU/mL at inclusion.

All volunteers will be recruited by the Surrey Clinical Research Centre, University of Surrey, England.

More centres may be included.

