The two antigens in C-Tb are also present in Tuberculin PPD RT 23 SSI. PPD has been used for 100 years in millions of people world-wide and has been found to be safe during pregnancy and lactation as stated in the Tuberculin PPD RT 23 SSIs currently approved SmPC for Denmark and Germany. C-Tb and Tuberculin PPD RT 23 SSI have comparable safety profiles and women of childbearing potential may be included in future phase III clinical trials with C-Tb without prior pregnancy testing.

For safety reasons the injections will be postponed 2 days if a volunteer on the day of injections has an oral temperature  $\geq 38.3$  °C, and/or if the volunteer is in treatment with analgesics/antipyretics. Furthermore, there will be at least 30 minutes between the injections to different volunteers. All volunteers will be observed for one hour after the injections by experienced study staff at the trial site. Immediate AEs, if any will be recorded in the CRF.

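### The QuantiFERON objective covers screening and day 28, but section 12.5 states an analysis for the screening values only, where a rank correlation is bounded low if few volunteers react to C-Tb

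*Protocol*

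**What the plan says.** Section 7.2 sets a secondary objective of comparing C-Tb induration with the in-vitro IFN-γ "response measured at screening and 28 days after the injections of the skin test agents". Section 7.4 names the matching endpoint from "blood samples taken at screening and 28 days after the injections of the skin test agents". The synopsis repeats both, and section 8.1 schedules the sampling: the "assay will be performed at the screening visit and on day 28".

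Section 12.5 then names one QFT analysis. Its sentence is limited to the inclusion values: these "Gold values are correlated with the C-Tb indurations by means of" Spearman's rank correlation, supplemented with scatter plots. Neither section 12.5 nor the statistical methods in the synopsis mention the day 28 values.

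Three other statements bear on this:

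- Section 8.2 admits only volunteers with an IFN-γ "result below 0.35 IU/mL at inclusion", and section 8.6 excludes anyone with a positive QFT at inclusion.
- Section 8.1 expects no skin reaction at the C-Tb site in this population, and the synopsis says the same.
- Section 8.1 also foresees conversion: "There is a small risk that this blood test can become positive during the trial due to the injected C-Tb skin test agent". Section 9.3.2 adds: "The two antigens in C-Tb are also present in Tuberculin PPD RT 23 SSI".

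**The concern.** The objective has two time points and the stated method has one. The one it keeps is restricted on both axes: QFT by the eligibility limit, and C-Tb by the expectation that nearly every reading is 0 mm. A low or undefined coefficient could then follow from the design alone and would say little about whether the two tests agree.

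The time point left out is the only one at which QFT is free to turn positive. The protocol takes that possibility seriously enough to arrange a six-month retest for anyone affected, yet plans no estimate of how often it happens and no comparison with the skin reading. At stake is a secondary objective that would be half reported, on the less informative half.

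**Working it through.** **Inputs.** From the protocol: n = 150 (section 8.3), inclusion QFT below 0.35 IU/mL (8.2), C-Tb induration not expected (8.1 and synopsis). The protocol gives no expected share of reactors and no figure for the QFT correlation, so the number of non-zero readings k is varied.

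**The protocol's own figure.** Section 12.6 gives a largest standard deviation of 0.041 for the estimated distribution function: √(0.5 × 0.5 / 150) = 0.0408. It reproduces, but it concerns specificity and has no bearing on QFT.

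**Ceiling on Spearman's coefficient.** Suppose the n QFT values are all distinct, k C-Tb readings are non-zero and distinct, and the other n − k tie at 0 mm. The largest coefficient, reached when the ordering agrees perfectly, is

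ρ_max = √(1 − [(n − k)³ − (n − k)] / (n³ − n)), with n³ − n = 3,374,850.

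| k | (n − k)³ − (n − k) | ρ_max |
|---|---|---|
| 0 | – | undefined |
| 1 | 3,307,800 | 0.14 |
| 3 | 3,176,376 | 0.24 |
| 5 | 3,048,480 | 0.31 |
| 15 | 2,460,240 | 0.52 |

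Tied QFT values change this. If m of the lowest QFT values are equal (m ≤ n − k), the ceiling is multiplied by 1 / √(1 − (m³ − m)/(n³ − n)). For m = 75 that is 1 / √(1 − 421,800 / 3,374,850) = 1.07, so 0.14, 0.24 and 0.31 become 0.15, 0.26 and 0.33. Heavier ties raise it further. The documents do not say how many ties to expect.

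**Chance that nobody reacts.** If the true share with any induration is p (assumed), all 150 read 0 mm with probability (1 − p)¹⁵⁰: 47% at p = 0.5%, 22% at 1%, 5% at 2%. The coefficient does not exist in those cases.

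**How far the result can still respond to the truth.** A simulation (600 runs per setting, two-sided 5% test) assumed a latent correlation of 0.5 between QFT and induration, and that eligibility removes the top 0, 5 or 20% of QFT values.

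| Share with any induration (assumed) | Power, 0% removed | 5% removed | 20% removed |
|---|---|---|---|
| 10% | 0.93 | 0.85 | 0.56 |
| 5% | 0.82 | 0.59 | 0.31 |
| 2% | 0.45 | 0.26 | 0.06 |
| 1% | 0.24 | 0.08 | 0.02 |

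**Precision available at day 28.** For 0 conversions in 150 the exact two-sided 95% upper limit is 1 − 0.025^(1/150) = 2.4%. For 3 in 150 the exact (Clopper-Pearson) interval is 0.4% to 5.7%. Both assume a day 28 result for all 150; dropouts would widen them slightly.

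**The case against.** The best defence is that section 12.5 is not the whole plan. It gives no method for adverse events or laboratory parameters either, and the primary specificity estimate with its interval is set out in the synopsis and section 12.6. A day 28 summary may sit in a statistical analysis plan that is not at hand, and silence on such detail is no error. This stands as far as it goes. But section 12.5 is not silent on QFT: it picks one of the two time points that the objective names and fixes a method for that one.

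A reader might infer that the screening correlation cannot answer its half of the objective, or would come out weak whatever the truth. The documents do not support that. The absence of induration is an expectation, and the trial exists to measure it. With 15 reactors the ceiling is 0.52, and simulated power can be high. Even 3 reactors allow 0.24, above the approximate 5% critical value of 1.96/√149 = 0.16. Values below 0.35 IU/mL can still be ranked, and the scatter plots would show individual outliers. Section 7.2 also asks for the screening comparison, so deleting it would open a new gap.

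A reader might further infer that the protocol would credit any conversion to C-Tb alone. The wording in sections 8.1 and 9.3.3 explains why a retest is offered and is not an analysis rule. The objective and endpoint already speak of the skin test agents, and the synopsis says the follow-up is meant to exclude tuberculosis infection. Section 9.3.2 gives no amounts of the two antigens in PPD, so a PPD effect on QFT is not established either.

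Finally, no stated objective asks for a conversion rate as such. That is true, which makes the conversion proportion a useful addition; the cross-tabulation against C-Tb is the part that answers section 7.2.

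**Conclusion.** The mismatch is real: objective and endpoint cover screening and day 28, and the stated analysis covers screening only. The gap at day 28 is plain on the text of the protocol, subject to whatever an unseen analysis plan adds.

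The weakness at screening is conditional. If the protocol is right that almost nobody reacts, the coefficient is capped at 0.14 to 0.31 for 1 to 5 non-zero readings (distinct QFT values assumed), or is undefined, and says little about agreement. If around 10% react it carries some information. Responder share, latent correlation, truncated share and the extent of ties are assumptions, because the documents give none of them.

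On attribution, the supportable statement is modest: every volunteer receives both agents at the same visit and there is no C-Tb-only group, so this trial cannot separate their effects on QFT. The point concerns a secondary objective. It is worth correcting and does not touch the primary estimate, the sample size or the data collected.

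**What to change.** In section 12.5:

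- Keep the screening correlation and scatter plot, labelled descriptive, and say that the coefficient will be reported as not estimable if no C-Tb reading is above 0 mm.
- Add a cross-tabulation of the day 28 QFT result (positive at 0.35 IU/mL or above, with indeterminate results shown separately) against C-Tb result at each candidate cut-off, and a day 28 scatter plot of IFN-γ against induration.
- Add the proportion converting from screening to day 28 with an exact 95% confidence interval, and optionally the paired change in IFN-γ.
- Describe conversion as following the skin test agents, not as an effect of C-Tb alone; sections 8.1 and 9.3.3 could be aligned with that wording.

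The cost is a few lines of text and one extra table. All the samples are already scheduled. If few volunteers react, the day 28 table will be sparse too, but its counts remain interpretable.
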